***Community questionnaire***

The purpose of the community questionnaire is to gather data on underlying factors at the community level, and to compare the different clusters over time. The community questionnaire also captures the causes of undernutrition that are embedded within the larger societal and environment factors. The community questionnaire was designed to provide information on the following aspects of each village in the sampling area:

- General characteristics of the village: population, percentage of minority and poor household, main source of income in peak and low seasons
- Infrastructure of the village: access to main road, electric, gas, and irrigation systems
- Distance from the nearest major town, type of transportation used to reach this town
- Natural disasters occurring in the village during the last year
- Presence of other organizations or support groups

**Ethical approval**

The evaluation has been approved by IFPRI’s Institutional Review Board, and the Bangladesh Medical Research Council in Bangladesh.

**Timeline for endline survey**

The survey timeline is depicted in the table below. As the baseline data collection was conducted starting on April 8, 2010, the endline data collection will also start that same week in 2014. The data collection schedule will be identical to that at baseline, to avoid seasonality effects for the same upazilas as best as possible. Data collection is scheduled to end by the end of June, 2014.

# STATISTICAL ANALYSIS PLAN

## Overall approach

The overall approach to the A&T impact analysis involves two major steps:

1. Accurately **estimate the impact** of the A&T-intensive interventions on IYCF practices and anthropometric outcomes
2. **Enhance plausibility** of impact estimates through:
   1. **Examining social desirability bias** for IYCF practices, especially for those practices (EBF) that are susceptible to systematic reporting bias
   2. Assessment of **biological plausibility** of changes in outcomes based on age of initial exposure and duration of exposure
   3. ***Impact pathway analysis*** that documents exposure to A&T interventions
   4. Analysis of ***trends in underlying determinants*** of IYCF practices and child growth, to rule out alternative reasons for trends over time

The overall analysis will examine and adjust, as needed, both for time invariant characteristics that can have impact on outcomes (i.e., geographic clustering) and time variant determinants where important changes were seen over time (e.g., women’s work patterns, food security, etc.).

The impact on exclusive breastfeeding (EBF) will be assessed in children 0-5.9 months old. The impact on other IYCF practices and anemia will be assessed in children 6-23.9 months old and the impact on stunting will be assessed in children 24-47.9 months old.

## Impact indicators

A&T’s core impact indicators are the 8 WHO-recommended IYCF indicators and child stunting. We will, however, examine impacts on all anthropometric indices – height-for-age, weight-for-age and weight-for-height. The indicators are depicted in Table 6 below:

**Table 6. Impact indicators**

| **Indicator** | **Age group (mo)** | **Remarks** |
| --- | --- | --- |
| ***Breastfeeding practices*** |  |  |
| Early initiation of breastfeeding | 0-23.9 |  |
| Exclusive breastfeeding under 6 months | 0-5.9 | We will also examine questions included in the endline survey that address social desirability bias |
| Continued breastfeeding at 1 year | 12-15.9 |  |
| ***Complementary feeding*** |  |  |
| Introduction of solid, semi-solid food, or soft food | 6-8.9 |  |
| Minimum diet diversity | 6-23.9 |  |
| Minimum meal frequency | 6-23.9 |  |
| Minimum acceptable diet | 6-23.9 |  |
| Consumption of iron-rich food | 6-23.9 |  |
| ***Anthropometry*** |  |  |
| HAZ | 24-47.9.9 | We will also examine impacts on HAZ among potentially fully exposed children (24-35.9 mo.) |
| Stunting | 24-47.9.9 | We will also examine impacts on HAZ among potentially fully exposed children (24-35.9 mo.) |

## Detailed statistical analysis approach

The statistical analyses will include intent-to-treat analyses, unadjusted and adjusted, for primary impact indicators. Several other analyses related to establishing plausibility of impacts will also be undertaken.

1. **Impact estimates**

Impact estimates in Bangladesh will be double difference estimates of changes in key impact indicators. This takes into account changes over time between baseline and endline in the intervention and comparison groups, and differences between groups at these times. The impact estimates will yield (1) **percentage point and percentage changes** for IYCF practices and stunting, wasting, and underweight, and anemia (Bangladesh only); and (2) change in **mean Z scores** for height for age, weight for age, weight for height, and hemoglobin (Bangladesh only).

Analyses will be done separately for each critical age group, e.g., exclusive breastfeeding will be assessed only in children 0-5.9 months old, complementary feeding in children 6-23 months old and anthropometry impacts in children 24 months and above. These reflect the different sample age groups for the impact evaluation. All analyses are in Stata.

Analyses will focus on the following:

- ***Pure* *Intent-to-treat*** analyses based on the original evaluation design and original age groups, using child-level data and fixed-effects analysis to achieve double difference estimates. The fixed-effects analysis will account for village, the smallest level repeated between baseline and endline. Further adjustment for geographic clustering at provincial/divisional, district and commune/subdistrict level will be done using random- or fixed-effects to adjust for clustering if needed; the need for this is not likely because of the accounting of variation among villages.
- ***Pure intent to treat in high potential for exposure age groups* –** this analysis will focus on the stunting indicator and capture impact estimates in an age group of children who are mostly likely, because of their age, to have been exposed to A&T’s interventions early in infancy and for the longest duration. This is the 24-35 month age group in both Bangladesh and Vietnam. We will examine the pattern of HAZ across the full 0-59 month age range, and look at impacts on stunting beginning at the age when HAZ begins leveling off i.e. possibly beginning at 18 months of age. We will use fixed-effects regression models to adjust for village clustering as above.
- ***Adjusted intent-to-treat* analysis** using data from the original ITT age groups but now adjusting for child age, child sex and other variables that might be different between the A&T-intensive and A&T-non-intensive age groups. We will use random- or fixed-effects regression models to adjust for geographic clustering.

1. **Plausibility analysis 1 – Examining social desirability bias**

Recognizing the potential role of social desirability bias in influencing reporting of nutrition behaviors, we plan to examine this within the A&T impact analysis in the following ways:

- Examine results of a diverse set of “trick” questions in the surveys that try and capture ways of triangulating findings on EBF and diet diversity (given both of these rely on the 24-hr recall of foods fed to the kids and the mothers might either under or over report in the recall instrument, depending on the child’s age group).  Estimates of IYCF indicators separately for groups that appear to be “fixing” their 24 hour recall responses. Examples include:
  - Asking elsewhere in the questionnaire (not the IYCF module) about availability of formula, feeding bottles, special bowl for the child, etc. “Child-specific” assets have been added into the household asset module, for instance, and we ask about books, toys and special feeding materials for the child.
  - In Bangladesh, include formula, tinned milk powder, and baby bottles in the consumption expenditure module
  - Ask to see all the things they use when they are feeding the babies, maybe – all bowls, plates, cups, bottles – and note this in a short observation
- Triangulate the 24-hr recall data from interviews with mothers by also examining data from the grandmother and father what foods the child ate in the last 24 hours. Triangulate in the analysis the concordance here.
- Examine data on stool frequency and consistency and urine frequency in the illness module (likely not very reliable because bigger threat to EBF is water in most places)
- Examine data from questions on social desirability tendencies

*Note: there is currently no way to correct for any situations where social desirability bias appears to be strong from the above assessment approach but we will report briefly the findings from these analyses as part of any impact papers.*

1. **Plausibility analysis 2 - based on biological plausibility and implementation plausibility (exposure to A&T interventions)**
   1. Examine **anthropometry outcomes by child age (**biological plausibility**) and duration of exposure** (intent to treat analysis for implementation plausibility).

- **Exposure variables** will include the following
  - FLW contact (use the question regarding # of contacts within the last 6 months))
  - Mass media exposure (use both the question of recall of ever having seen specific ads, with recall of at least x number of messages in the ad, or select messages )
  - Franchise contact (VN)
  - **MNP purchase and consumption variables (Bangladesh only)**
    - 1. Every purchase
      2. Total number in the last 6 months
      3. Consumption in last 7 days
- **Plausibility analysis based on impact pathways**
  - Is exposure to A&T interventions greater in A&T-intensive areas?
  - Are IYCF and nutrition knowledge, especially of key messages promoted by the program (“content tracers”) greater in A&T-intensive areas?
  - Are other behavioral determinants more conducive to behavior change in A&T-intensive areas?
  - Is intensity of intervention exposure associated with IYCF? practice/anthropometry outcomes, controlling for confounding factors?
- **Plausibility analysis based on underlying determinants of IYCF/anthropometry:**
  - Are there any systematic differences in underlying determinants of IYCF practices and anthropometric outcomes over time or across groups, such that *differential changes* in those underlying determinants over time offer alternative explanations for changes in IYCF or anthropometric outcomes? For example:
    - In Bangladesh, have there been changes in food security over time, and across groups, that might drive some of the changes in diet diversity?
    - In Vietnam, have there been differential changes in women’s work patterns over time and across groups, in ways that might shape EBF practices differently?
  - This analysis – assessing changes and then adjusting statistically for those underlying differences where changes are seen – will adjust for *time-variant* factors that changed over time.   The geographic clustering in the DID model only adjusts for time *invariant* changes over time.

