In Bangladesh, 100 sub-districts, across five of six divisions, were selected by BRAC as possible A&T intensive areas based on high poverty and stunting levels, and sub-districts that were not included in the government National Nutrition Program. This list was narrowed to 78 based on geographic proximity, size, and other operational aspects to ensure homogeneity across the sample. Within each division, four sub-districts were then randomly selected for inclusion in the evaluation sample using a computer program, for a total of 20 sub-districts. Sub-districts within each division were then randomly assigned, using a computer program, to either the *intensive* (10 sub-districts) or *non-intensive* (10 sub-districts) intervention. The randomization process was carried out in the presence of BRAC and A&T staff and the program evaluators in BRAC’s headquarters in Dhaka.

The baseline survey was conducted in 20 rural *upazilas* that are part of BRAC’s Essential Health Care (EHC) program platform for A&T. The baseline survey had three components—(i) household survey, (ii) community survey, and (iii) staff survey.

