# Annex 2. Randomization of upazila for Alive & Thrive baseline study in BRAC EHP areas

| **District** | **Name of *upazilas*** | **Randomized to** |
| --- | --- | --- |
| ***Dhaka Division*** | | |
|  | Hossainpur | A&T |
|  | Pakundia | A&T |
|  | Sonargaon | No A&T |
|  | Araihazar | No A&T |
| ***Chittagong Division*** | | |
|  | Sonagaji | No A&T |
|  | Dagonbhuian | No A&T |
|  | Sonaimuri | A&T |
|  | Kompaniganj | A&T |
| ***Rajshahi Division*** | | |
|  | Nandigram | A&T |
|  | Kahalu | A&T |
|  | Parbatipur | No A&T |
|  | Chirirbandor | No A&T |
| ***Khulna-Barisal Division*** | |  |
|  | Damurhuda | A&T |
|  | Alamdanga | A&T |
|  | Bheramara | No A&T |
|  | Daulatpur | No A&T |
| ***Sylhet Division*** | | |
|  | Madhapur | A&T |
|  | Lakhai | A&T |
|  | Jointapur | No A&T |
|  | Goainghat | No A&T |

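### Upazilas were randomised within division, two against two, but no intention-to-treat double-difference model carries a division-by-round term, so division trends would stay in a valid upazila-level standard error

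*Combined protocol and SAP*

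**What the plan says.** **Design.** The section EVALUATION DESIGN describes sampling and allocation by division: "Within each division, four sub-districts were then randomly selected for inclusion in the evaluation sample", and then "Sub-districts within each division were then randomly assigned, using a computer program". Annex 2, "Randomization of upazila for Alive & Thrive baseline study in BRAC EHP areas", lists five blocks (Dhaka, Chittagong, Rajshahi, Khulna-Barisal, Sylhet). Each holds four upazilas, two marked A&T and two marked No A&T.

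**Analysis.** Under Detailed statistical analysis approach, the pure intention-to-treat estimate is a double difference on child-level data: "The fixed-effects analysis will account for village, the smallest level repeated between baseline and endline". Higher levels are conditional: "Further adjustment for geographic clustering at provincial/divisional, district and commune/subdistrict level will be done using random- or fixed-effects to adjust for clustering if needed". The plan expects not to use them: "the need for this is not likely because of the accounting of variation among villages". The analysis in the high-exposure age group uses the same village approach. The adjusted analysis adds child age, sex and other covariates, with random or fixed effects for geography. None of the three includes an interaction of division with survey round.

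**What the geographic terms do.** The plausibility part of the same section says: "The geographic clustering in the DID model only adjusts for time", and the sentence goes on to specify time-invariant factors. Time-varying adjustment there and under Overall approach covers measured determinants that are seen to change, not division trends as such.

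**The concern.** Division is the stratum within which upazilas were randomised, yet it does not enter the double difference in the one form that would matter there. A double difference compares changes, so constant differences between divisions have already gone. What remains is the possibility that outcomes moved differently by division over four years. The design balances such movement across arms exactly, and the analysis can therefore remove it.

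If it is left in, a correct analysis of 20 upazilas treats it as noise. With 10 units per arm, precision is scarce: Table 3 says that detecting a 9 rather than a 10 percentage point (pp) difference in stunting would need double the sample.

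**Working it through.** **The plan's own figure.** The stunting sample of 1,100 per arm (43% to 36.5%, ICC 0.005, 20 clusters, 0.05 level, 80% power) has a design effect of 1 + (110 − 1) × 0.005 = 1.545.
- One-sided 0.05: 700 × 1.545 = 1,082, close to 1,100.
- Two-sided 0.05: 889 × 1.545 = 1,374.

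The calculation makes no use of division, so it neither supports nor contradicts this point. The intervals below are two-sided 95%.

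**Inputs.** From the documents: 20 upazilas, 5 divisions, 2 v 2 in each. Assumed: sd² is the between-division variance of change, sw² is the variance of upazila change within division (including child sampling error), and s = sd²/(sd² + sw²).

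**Step 1, bias.** Each division contributes two upazilas to each arm, so its trend enters both arm means with equal weight and cancels. The true variance of the estimate is sw² × (1/10 + 1/10), whatever sd² is.

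**Step 2, estimated error from 20 upazila changes.**
- Without division-by-round: 20 − 2 = 18 df. Expected residual mean square = [4(sw² + 4sd²) + 14sw²]/18 = sw² + (16/18)sd².
- With it: 20 − 5 − 1 = 14 df. Expected residual mean square = sw².

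**Step 3, interval width, without/with.** Ratio = (2.101/2.145) × √(1 + (16/18) × s/(1 − s)).

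| s (assumed) | Ratio | Effect of adding the term |
|---|---|---|
| 0% | 0.98 | about 2% wider |
| 5% | 1.00 | none |
| 10% | 1.03 | 2.6% narrower |
| 30% | 1.15 | 13% narrower |
| 50% | 1.35 | 26% narrower |

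Break-even: sd²/sw² = [(2.145/2.101)² − 1]/(16/18) = 0.047, so s = 0.047/1.047, about 4.5%.

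**Step 4, stunting scale.** Table 3 gives prevalence 50.9% and upazila ICC 0.02; 1,100/10 = 110 children per upazila per round. Assume a cluster autocorrelation of 0.8 between rounds, with division trend added on top.

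sw² = 2(0.2499)(0.02)(0.2) + 2(0.2499)(0.98)/110 = 0.00200 + 0.00445 = 0.00645.

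- Half-width with the term: 2.145 × √(0.00645 × 0.2) = 7.7 pp.
- Without it: 7.5, 8.3 and 10.4 pp for division-trend SDs of 0, 4 and 8 pp.
- At autocorrelation 0.5: 9.3 pp with the term; 9.1, 9.8 and 11.6 pp without.

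**Step 5, simulation.** Settings: 4,000 runs each; 20 upazilas × 10 villages × 11 children per round; upazila-trend and village-trend SDs of 5 pp (assumed).

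| Division-trend SD | Upazila level, no term: coverage (half-width) | Upazila level, with term: coverage (half-width) |
|---|---|---|
| 0 pp | 94.9% (7.9 pp) | 95.0% (8.05 pp) |
| 4 pp | 96.7% (8.6 pp) | 95.1% (8.04 pp) |
| 8 pp | 98.6% (10.6 pp) | 95.1% (8.07 pp) |

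The empirical SD of the estimate stayed at about 3.8 pp throughout, which confirms Step 1. The model with village fixed effects and no upazila-level error covered only about 88–89%, with a half-width of 5.9 pp.

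**The case against.** The strongest objection is that the plan as written does not suffer this loss. It commits to village fixed effects on child-level data, not to upazila-level inference. A reader might infer that the planned intervals are too wide; the documents do not support that. On the simulation above the village-only intervals are too narrow, and the loss described here arises only once that larger problem is put right. This stands, and it is why the term should come with upazila-level inference.

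A reader might also infer that the fault lies in making divisional adjustment conditional on need. It does not. A division main effect is already absorbed by the village effects, so making it mandatory would change nothing. Only the interaction with round matters.

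The gain is also uncertain and may be small. The variance of an observed upazila change includes child sampling error. Suppose Table 3's stunting ICC of 0.02 already includes division differences. Even if all true variation in change lay between divisions, s could then not exceed 0.00200/0.00645 = 31% at autocorrelation 0.8, or 53% at 0.5. If a fifth of it did, s would be about 6–11% and the gain about 1–3%. Table 3 gives larger ICCs for HAZ (0.05) and EBF (0.12), which leave more room. For anemia it gives 0.00, where the term would only cost degrees of freedom.

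Finally, repeating the baseline calendar and adjusting for measured time-varying determinants may shrink division trends. Neither replaces the stratum term.

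**Conclusion.** The point holds as one of efficiency and of matching the analysis to the allocation. The randomisation stratum is not carried into the double difference, and the plan's reason for expecting no further adjustment, that village variation is accounted for, does not reach trends.

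It is not a point about bias: a reader might infer that omitting the term distorts the impact estimate, but the two-against-two allocation in Annex 2 rules that out for division trends. At upazila level, omitting the term makes intervals conservative when division trends exist.

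The size rests on an assumed s, for which the documents give no figure, so no definite gain can be claimed. The range runs from about 2% wider (s = 0) to 13% narrower (s = 30%) and 26% narrower (s = 50%). Confidence is high on the omission and the mechanism, and limited on the amount. The change is still worth making because the possible cost is small and fixed.

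**What to change.** In Detailed statistical analysis approach:

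1. State that division, as the five blocks of Annex 2, is the randomisation stratum.
2. Include division-by-round fixed effects in the double-difference intention-to-treat models (pure, high-exposure age group and adjusted), together with upazila-level inference on about 14 df. Specify both before the endline data are analysed, so that the choice of geographic terms does not depend on results.
3. If a permutation test is used, reallocate only within division: C(4,2)⁵ = 6⁵ = 7,776 possible allocations.

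The conditional wording on the division main effect needs no change on this account.

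Cost: a line or two of SAP text, one model term and 4 degrees of freedom; at worst, intervals about 2% wider than an unstratified upazila-level analysis would give. No change to data collection.

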## Sample size and power calculations

Sample sizes were estimated based on detectable differences between A&T and non-A&T *upazilas* for three separate sets of indicators: 1) exclusive breastfeeding (EBF) rates, 2) complementary feeding practices, and 3) stunting. Our sample size estimates accounted for randomization at the cluster (i.e., *upazila*) level rather than at the individual level. Surveys are repeated cross-sectional, surveying different households/children from the same communities.

The estimated sample sizes for each treatment arm, calculated prior to the baseline survey, was 500 infants 0-5.9 months old for EBF, 500 children 6-23.9 months old for complementary feeding-related practices, and 1,100 children 24-47.9 months old for stunting. Thus, the total proposed sample size was 4,200 children 0-47.9 months old. This sample size was estimated to allow us to detect expected differences in the outcomes outlined below, in a total of 20 clusters with an inter-cluster correlation (ICC) of 0.005, a significance level of 0.05, and power of 80 percent.

A sample size of 500 children aged 0-5.9 months of age was deemed sufficient to detect an increase in EBF rates by approximately 49 percent (from 43 percent to 64 percent); a sample size of 500 children aged 6-23.9 months of age is sufficient to detect an increase in several complementary feeding practices by at least 25 percent; a sample size of 1,100 children aged 24-47.9 months of age is sufficient to detect a reduction in stunting by 15 percent (from 43 percent to 36.5 percent).

Detailed sample size calculations are presented in **Table 3**.

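### The impact model rests on village fixed effects and expects no sub-district adjustment, although upazilas were randomised; false-positive rates can be well above 5% if outcomes change differently across upazilas

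*Combined protocol and SAP*

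**What the plan says.** - **Unit of randomisation.** Under Evaluation Design: "Sub-districts within each division were then randomly assigned, using a computer program". There are 10 upazilas per arm. Annex 2 shows five divisions with two upazilas per arm in each.
- **Sample size.** Under Sample size and power calculations: "Our sample size estimates accounted for randomization at the cluster", with the upazila named as the cluster, and the target differences stated "in a total of 20 clusters with an inter-cluster correlation (ICC) of 0.005". Table 3 then reports baseline upazila ICCs of 0.12 (EBF), 0.05 (HAZ), 0.04 (minimum acceptable diet), 0.02 (stunting) and 0.00 (anemia).
- **Main model.** Under Detailed statistical analysis approach, the pure intention-to-treat (ITT) analysis uses child-level data and village fixed effects. Random or fixed effects for sub-district and higher levels are to be added only if needed, and "the need for this is not likely because of the accounting of variation among villages".
- **Other ITT analyses.** The analysis of the age group with high potential exposure adjusts for village in the same way. The adjusted ITT promises adjustment for geographic clustering but names no level.
- **The plan's own caveat.** Later in the same section: "The geographic clustering in the DID model only adjusts for time"-invariant factors.

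No type of standard error, upazila-by-round term or small-cluster correction is given.

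**The concern.** Treatment is assigned to whole upazilas, and the impact estimate is an arm-by-round contrast. Anything that moves all children of one upazila together between 2010 and 2014 (a local shock, another program, local supervision) is the noise against which the treatment must be judged. A village intercept cancels what is constant in a village. It does not cancel a change shared by all ten sampled villages of an upazila. The stated reason for expecting no sub-district adjustment therefore does not follow, and it conflicts with the plan's own remark on what the geographic terms can do.

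The fallback is no safeguard if it means sub-district intercepts, because the village effects already absorb them. At stake are the confidence intervals and p-values for both stated hypotheses, on feeding practices and on stunting. Ordinary variation between upazila trends could be reported as program impact.

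**Working it through.** **Step 1: the plan's own figure.** Table 3 gives 920 for stunting, 50.9% against 40.9% (10 points), ICC 0.02. Two proportions at one-sided 5%, 80% power and with continuity correction need 326 per arm under individual sampling. With k = 10 clusters per arm:

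k·n·(1 − ICC)/(k − n·ICC) = 10 × 326 × 0.98/(10 − 6.52) = 918.

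So the sample size does treat ten upazilas per arm as the limiting unit. (The two-sided version gives 2,202. The plan does not state sidedness, and that is a separate matter.)

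**Step 2: inputs.** Planned children per arm and round are 500 for EBF, 500 for minimum acceptable diet and 1,100 for stunting and HAZ. Over 10 upazilas, m = 50 or 110 per upazila and round. ICCs are from Table 3. Assumption not in the documents: r, the correlation of upazila effects between the two rounds, shown from 1 down to 0.5.

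**Step 3: formula.** With total variance 1 and n = 10m, stable upazila effects cancel in the double difference, leaving:

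- true variance: 4·[(1 − r)·ICC/10 + (1 − ICC)/n]
- variance assumed by the village fixed-effects model: 4·(1 − ICC)/n
- ratio: V = 1 + m·ICC·(1 − r)/(1 − ICC)
- true type I error of a nominal two-sided 5% test: 2·P(Z > 1.96/√V)

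Example, EBF at r = 0.8: V = 1 + 50 × 0.12 × 0.2/0.88 = 2.364, √V = 1.54, 1.96/1.54 = 1.27, error 20%.

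Example, stunting at r = 0.8: V = 1 + 110 × 0.02 × 0.2/0.98 = 1.449, √V = 1.20, error 10%.

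**Step 4: results, model-based standard errors.**

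| Outcome (ICC) | r = 1 | 0.95 | 0.9 | 0.8 | 0.5 |
|---|---|---|---|---|---|
| EBF (0.12) | 5% | 9% | 13% | 20% | 35% |
| HAZ (0.05) | 5% | 8% | 12% | 18% | 32% |
| Stunting (0.02) | 5% | 6% | 8% | 10% | 18% |
| Minimum acceptable diet (0.04) | 5% | 6% | 7.5% | 10% | 17% |
| Anemia (0.00) | 5% | 5% | 5% | 5% | 5% |

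The error reaches 10% when V = (1.96/1.645)² = 1.42, that is when 1 − r = 0.42·(1 − ICC)/(m·ICC). This is about 6% for EBF, 7% for HAZ, 19% for stunting and 20% for minimum acceptable diet.

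**Step 5: village-clustered errors.** In a simulation (normal outcomes, 10 upazilas of 10 villages per arm, two rounds, 3,000 runs per setting), clustering on village at r = 0.5 still gave 29% (EBF), 27% (HAZ), 16% (stunting) and 15% (minimum acceptable diet).

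**Step 6: stratification.** A change shared by a whole division cancels between arms. If half of the round-specific variance lies between divisions (assumed), EBF at r = 0.5 has V = 1 + 50 × 0.12 × 0.5 × 0.5/0.88 = 2.705 and an error of 23% instead of 35%.

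**Step 7: the remedy.** With no division variance, a t test on the 20 upazila changes (18 df) had a simulated error of 4.4% to 6.4%. Upazila-level variance with a normal reference and no small-sample correction gave about 7% to 9.5%. With the half-share of Step 6 (EBF and HAZ, r = 0.5), the unstratified 18-df test was conservative at about 2%. Including division, with 20 − 5 − 1 = 14 df, gave about 5%.

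**The case against.** The strongest reply is that the inflation is conditional and the plan is not closed.

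- **r is unknown.** At r = 1 there is no inflation, and at r = 0.95 stunting and minimum acceptable diet sit near 6%. The endline repeats the baseline fieldwork calendar for the same upazilas, which favours a high r. This stands, so a reader should not infer that false-positive rates are certain to be far above 5%. But the plan itself collects data on economic shocks, food security, natural disasters and other organizations because it expects conditions to change, so r = 1 cannot be presumed.
- **Sub-district adjustment is left open and no type of standard error is stated.** This also stands. A reader might infer that upazila-level inference has been ruled out; the text does not say so. It does give a wrong reason for expecting not to need it and no criterion for when it would be needed, so the choice could be made after results are seen.
- **Stratification lowers the figures.** Correct. In that respect the table shows upper values for each r.
- **Time-varying covariates will be adjusted for.** They may absorb part of the shared change, but they do not replace inference at the randomised unit.

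Annex 2 lists same-arm upazilas next to each other, from which a reader might infer that pairs were drawn. The documents do not support that: Evaluation Design describes sub-districts being assigned, and row order grouped by arm is not evidence of paired drawing.

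**Conclusion.** The rule is wrong as written and should be changed before analysis. Village fixed effects do not account for upazila-specific change, and sub-district intercepts would not either. With model-based or village-clustered standard errors, uncertainty will be understated if outcomes change differently across upazilas.

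The size depends on r, which the documents do not give. Between r = 0.95 and r = 0.5 the true rate of a nominal 5% test with model-based errors runs from 9% to 35% for EBF, 8% to 32% for HAZ, and about 6% to 17 or 18% for stunting and minimum acceptable diet. It is 5% at r = 1, and anemia is unaffected at its reported ICC. The figures take the Table 3 ICCs and planned sample sizes as given. The design fault is certain; its numerical size is not.

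**What to change.** Replace the sentence on sub-district adjustment, for the pure, high-exposure and adjusted ITT analyses alike, by:

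> All impact estimates use inference at the unit of randomisation: standard errors clustered on upazila (both rounds in one cluster), with division-by-round terms to reflect the stratified randomisation and a t reference with about 14 df, or equivalently an analysis of the 20 upazila-level changes adjusted for division, confirmed by a permutation test over the 6^5 = 7,776 within-division allocations.

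(Each division has 6 ways to choose two of four upazilas, and there are five divisions.) Village fixed effects may stay for the point estimate.

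The cost is SAP wording, a little more analysis work for the division terms and the permutation test, and wider confidence intervals where upazila trends differ. No new data are needed.
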